## Abstract

**Introduction:**

Metabolic bariatric surgery (MBS) can lead to substantial fat-free mass loss (FFML) due to malnutrition, decreased protein intake and insufficient physical activity. Disproportional FFML has been associated with an increased risk for adverse health outcomes. Resistance training (RT) combined with protein intake contributes to maintenance and increase of fat-free mass (FFM) in healthy individuals. However, it is unclear whether RT and protein supplementation can prevent FFML after MBS.

**Methods and analysis:**

In the EffectiveNess of pRotein supplementatIon Combined witH resistance Exercise training to counteract Disproportional fat-free mass loss following metabolic bariatric surgery (ENRICHED) randomised controlled trial, 400 patients scheduled to undergo MBS will be randomised in a 1:1 ratio to the ENRICHED perioperative care programme (intervention group) or the standard perioperative care programme of the Dutch Obesity Clinic (control group). The study is currently recruiting participants at two centres in the Netherlands: Nieuwegein and Amsterdam. The postoperative standard programme consists of 13 group sessions spread over a period of 18 months. As part of the ENRICHED programme, RT and protein supplementation will be added 3 weeks after MBS. Additional whole-body RT consists of home-based training sessions two to three times a week, and supervised RT sessions of 45–60 min once weekly, performed at 60–75% of one-repetition maximum (1-RM). Protein supplementation will start by adding 20 g of whey protein to the daily intake. The supplementation will be gradually increased with 20 g every 4 weeks until a total of 60 g whey protein a day is reached. After 12 weeks of protein supplementation, the focus shifts towards incorporating protein-rich food products into the daily dietary intake. The primary endpoint is the prevalence of disproportional FFM loss, defined as FFML/total weight loss ≥30%, at 3 months post-MBS. Secondary endpoints are differences in body composition, muscle strength and function, cardiorespiratory fitness, (cardio)metabolic health, health-related quality of life, gastrointestinal discomfort, cost-effectiveness of the intervention and treatment satisfaction. Outcomes will be assessed preoperatively and at 3, 6 and 12 months postoperatively.

**Ethics and dissemination:**

The study protocol V.2.0 was approved by the Medical Research Ethics Committee Oost-Nederland (NL-OMON57119) on 9 April 2025. All participants will provide written informed consent prior to enrolment. Study findings will be disseminated through peer-reviewed publications and conference presentations. Insights gained in this study will provide evidence for a patient-tailored intervention that could be implemented in clinical practice.

**Trial registration number:**

NCT07156552.

STRENGTHS AND LIMITATIONS OF THIS STUDYThis is a large-scale, multicentre randomised controlled trial to evaluate the combined effect of resistance training and protein supplementation on fat-free mass preservation in the early postoperative phase after metabolic bariatric surgery.The intervention is embedded in routine clinical care, enhancing feasibility, adherence and potential implementation in clinical practice.Objective measurements of physical activity, body composition and dietary intake provide comprehensive outcome data.Blinding of participants, healthcare providers and researchers is not feasible due to the nature of the intervention, which may introduce performance bias.Although dual-energy X-ray absorptiometry is the gold standard for body composition assessment, it is only used in a subgroup (n=100) due to cost and feasibility constraints.

## Introduction

 Obesity has become a pressing global health challenge, with its prevalence and severity continuing to rise across populations worldwide.^1^ Metabolic–bariatric surgery (MBS) is one of the most effective long-term interventions for the treatment of severe obesity, with a total weight loss (TWL) around 30% at 12 months postsurgery.^2^ In addition to weight reduction, MBS has been shown to be effective in improving metabolic health and reducing obesity-associated complications, thereby enhancing overall health-related quality of life (HRQoL).^3 4^

Despite these benefits, weight loss following MBS comprises not only fat mass (FM) but also a considerable proportion of fat-free mass (FFM). Studies have shown that approximately 25% of the TWL within the first 3 months post-MBS consists of FFM.^5^ FFM plays a crucial role in key physiological functions, including glucose metabolism, resting energy expenditure, thermoregulation and physical capacity.^6^ In turn, disproportional loss of FFM has been associated with impaired metabolic health and functional capacity, and an increased risk for chronic diseases ultimately leading to lower HRQoL.^47^,^9^ In the present study, we define a proportion of FFM loss (FFML) ≥30% as disproportional, based on previous evidence linking this ratio of FFML/TWL to an increased risk of major adverse cardiovascular events and mortality.^10^ The insights in the health consequences of FFML have shifted treatment goals in obesity treatment, coming from maximising weight loss to improving body composition and thereby general health.^11^

Resistance training (RT) complemented with protein supplementation has been shown to be effective for maintaining and improving FFM in healthy^12^ and clinical populations.^13^ However, patients post-MBS often fail to meet the daily recommended protein intake of 60 g/day^14^ and physical activity (PA) levels of 150 min of moderate-intensity PA.^15 16^ Evidence of the effectiveness of RT and protein supplementation in the early postoperative phase (3–12 months) following MBS remains limited. Previous studies have been rather small and involved homogeneous populations,^17^ or have focused solely on the late postoperative period (2–7 years post-MBS), with inconsistent findings.^18 19^

The ‘EffectiveNess of pRotein supplementatIon Combined witH resistance Exercise training to counteract Disproportional fat-free mass loss following metabolic bariatric surgery (ENRICHED)’ study aims to evaluate the effectiveness of RT complemented with protein supplementation in the standard perioperative care programme to counteract disproportional FFML in the first 3–12 months following MBS. Additionally, the effect of the intervention on body composition, (cardio)metabolic health, muscle strength and function, cardiorespiratory fitness, HRQoL, dietary protein intake and habitual PA patterns will be evaluated.

## Methods and analysis

### Study design

The ENRICHED study is a multicentre randomised controlled trial (RCT) with two parallel arms evaluating the effectiveness of a combined intervention of RT and protein supplementation (figure 1).

**Figure 1 F1:**
[figure not shown]
Schematic overview of the ENRICHED trial timeline and study procedures. DXA, dual-energy X-ray absorptiometry; ENRICHED, EffectiveNess of pRotein supplementatIon Combined witH resistance Exercise training to counteract Disproportional fat-free mass loss following metabolic–bariatric surgery; FFQ, Food Frequency Questionnaires; g, gram; GSRS, Gastrointestinal Symptom Rating Scale; OBESI-Q, a validated patient reported quality of life measure for patients with obesity PA, physical activity; RT, resistance training; VO_2_ Max, maximum uptake of oxygen.

### Study setting and recruitment

This study is currently being conducted at two centres of the Nederlandse Obesitas Kliniek (NOK, Dutch Obesity Clinic), located in Nieuwegein and Amsterdam, in the Netherlands. The NOK consists of a national network of 10 sites throughout the Netherlands which provide a perioperative care programme for patients undergoing MBS. Patients qualify for the perioperative care programme in accordance with the International Federation for the Surgery of Obesity and Metabolic Disorders criteria; body mass index (BMI) ≥40 kg/m^2^ or BMI ≥35 kg/m^2^ in combination with obesity associated diseases (eg, type 2 diabetes or hypertension).^20^ Both Roux-en-Y gastric bypass (RYGB) and sleeve gastrectomy (SG) procedures are included in this trial to enhance generalisability of our findings and to allow examining whether the intervention is effective across both surgical techniques.

Recruitment of participants began in May 2025 and is expected to continue until December 2026. Patients are verbally informed about the study by the treating healthcare professional during the intake consultation at the participating centres. If patients provide their permission to be contacted for further information, a member of the research team evaluates eligibility via the electronic health record and contacts the patients to discuss potential participation. Inclusion and exclusion criteria are summarised in table 1.

**Table 1 T1:** Inclusion and exclusion criteria

Inclusion criteria	Exclusion criteria
Scheduled to undergo RYGB or SG in one of the participating centres.	Allergic or sensitive to milk proteins, or lactose intolerant.
Age ≥18.	Diagnosed renal insufficiency (ie, eGFR <30 mL/min).
Able to understand and perform the study procedures.	Diagnosed intestinal diseases influencing uptake of protein (ie, active inflammatory bowel disease, Crohn’s disease).
	Inability to perform any resistance exercises (eg, severe physical limitations).
	Previous metabolic–bariatric surgery.
	Presence of medical devices (ie, pacemaker, neurostimulator) which are contraindicated for bioelectrical impedance analysis.

eGFR, estimated glomerular filtration rate; RYGB, Roux-en-Y gastric bypass; SG, sleeve gastrectomy.

### Randomisation, blinding and treatment allocation

A total of 400 patients will be enrolled and randomly assigned in a 1:1 ratio to either the intervention or control group. Randomisation will be stratified by sex to ensure a balanced sample across both groups, which does not imply equal representation of men and women. A computerised randomisation system (Castor Electronic Data Capture (EDC), Castor, Amsterdam, the Netherlands) will be used with variable block sizes of 16 and 24 to ensure allocation concealment. A subgroup of 100 patients will undergo additional measurements, including dual-energy X-ray absorptiometry (DXA) for body composition assessment and objective PA measurements using thigh-worn accelerometry. Blinding of the patients, involved healthcare professionals and outcome assessors is not possible due to the nature of the intervention.

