##### Intervention: home-based and supervised RT

Patients in the intervention group will receive an adapted version of the home-based RT protocol that is part of the standard care. This adapted protocol includes four difficulty levels with six adjusted whole-body RT exercises to ensure activation of all major muscle groups (online supplemental table 1). In the intervention protocol, each exercise is completed after four sets of 8–12 repetitions, with 60 s of rest between sets. All exercises in the home-based RT protocol can be performed using no to little equipment to ensure an easy translation to the home environment.

As part of the intervention, weekly RT sessions are provided at the clinic and are supervised by an experienced kinesiologist. The supervised RT protocol includes four machine-based whole-body exercises and one exercise using body weight (online supplemental table 2A). During the first supervised session, the kinesiologist will guide patients through the home-based RT protocol to ensure they understand how to perform the home-based exercises correctly and safely. During the second supervised session, patients are familiarised with the exercises of the supervised RT protocol and the one repetition maximum (1-RM) will be assessed for each exercise. If the kinesiologist considers that a reliable 1-RM assessment cannot be performed in a participant, the participant is instructed to perform the exercises based on perceived exertion using the 6–20 Borg rating of perceived exertion scale.^21^ Patients are familiarised with the scale before enrolment to RT. All participants are instructed to train at a Borg score between 12 and 14, corresponding to ‘somewhat hard’. During the following sessions, the prescribed training scheme (online supplemental table 2B) serves as a basis, progressing from three sets of 10–14 repetitions at 60% of the 1-RM to three sets of 8–10 repetitions at 75% of 1-RM. Adjustments to this scheme can be made according to the Borg scores to ensure that participants consistently train within the target range of Borg scores 12–14. Each set of exercises is performed with a lifting cadence of 1 s concentric and 1 s eccentric contraction with 60 s of rest between each set.^22^ During the 12th session, the 1-RM will be reassessed to prescribe RT for the remaining sessions.

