### Outcome measures

The primary outcome is the difference in proportion of patients with disproportional FFML/TWL (ie, ≥30%) in the intervention group compared with the control group at 3 months post-MBS. Secondary outcomes are postintervention differences in body composition, muscle strength and function, cardiorespiratory fitness, (cardio)metabolic health, HRQoL, gastrointestinal discomfort, cost-effectiveness of the intervention and treatment satisfaction in the intervention group. Most outcomes are measured preoperatively and at 3, 6 and 12 months post-MBS. Cost data are assessed preoperatively and at 6 and 12 months post MBS, and treatment satisfaction is assessed after the 6-month intervention period. Cost and outcome data are used to calculate the incremental cost-effectiveness of the intervention in terms of cost per successfully treated patient using a time horizon of 1 year.

The primary outcome was set at 3 months post-MBS as previous studies have shown that the most pronounced changes in body composition, including substantial reduction in FFM, occur during this early postoperative phase.^5 23^ Our intervention, combining RT and protein supplementation, was specifically designed to target this critical period. Secondary outcomes will be assessed at 6 and 12 months to assess the persistence of potential effects over time.

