### Questionnaires

After each measurement visit (ie, baseline, 3, 6 and 12 months postoperatively), participants will receive an email with a personal weblink to an online questionnaire (Castor EDC, Castor) to assess HRQoL and gastrointestinal symptoms and a separate weblink to an online Food Frequency Questionnaire (FFQ tool, Wageningen University and Research, Wageningen, The Netherlands). In addition to the online questionnaires, a brief set of structured questions will be asked in person during each measurement visit. These questions address current engagement in RT (eg, type of exercise and frequency), weekly performance of light, moderate and vigorous PA and prior use of glucagon-like peptide 1 receptor agonists for weight loss.

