#### Health-related quality of life

HRQoL will be evaluated using the OBESI-Q, a translated subset of the BODY-Q questionnaire, a validated patient-reported outcome instrument that is especially designed to measure a patient’s perception on weight loss and/or body contouring.^31^ The OBESI-Q questionnaire is designed to evaluate HRQoL in patients with obesity through 54-point Likert-scale (*Completely disagree* to *Completely agree* or *Never* to *Always*) questions, divided over five subscales: *eating behaviour, social function, psychological function, physical function* and *body image*. For each subscale, a sum score will be calculated. As part of the standard perioperative care at the NOK, patients are asked to fill in the OBESI-Q at baseline and after 12 months of follow-up. These data will be extracted from the electronic health record. A shortened version of the OBESI-Q will be sent from Castor EDC at 3 and 6 months postoperatively, including the subscales eating behaviour, physical function and body image, as we anticipate observing the most pronounced changes within these domains in response to our intervention.

In addition to the OBESI-Q, the five-level EuroQol five-dimensions (EQ-5D-5L) questionnaire will be administered orally during each measurement visit to assess HRQoL. The EQ-5D-5L is a validated instrument suitable for use in cost-effectiveness analyses.^32 33^

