Limitations observed in previous studies have been low compliance to protein intake protocols, potentially due to gastrointestinal discomfort and lacking information on habitual PA patterns.^43^ The protein supplementation protocol in the ENRICHED trial is based on recent findings that consumption of whey protein resulted in the highest increase in overall daily protein intake, compared with other types of protein supplementation strategies.^44^ Additionally, whey protein was found superior to other types of protein, such as soy, casein or hydrolysed collagen proteins, to increase muscle protein synthesis.^45^ Adherence to the ENRICHED protocol is closely monitored, enhancing the interpretation of the true effect of the intervention. Moreover, the intervention is embedded in the standard perioperative care programme.

In addition to clinical outcomes, the ENRICHED trial includes a cost-effectiveness analysis to evaluate the economic impact of the intervention. By combining quality-adjusted life years (QALYs) with data on healthcare consumption costs, this analysis will provide valuable insights into the potential for the implementation of the intervention in routine care.

The present study could have several strengths, including its multicentre design, large sample size and implementation of the intervention into a routine clinical setting. However, some limitations should be acknowledged. First, blinding of participants and care providers is not possible due to the nature of the intervention, which may introduce performance bias. Second, although DXA measurements are considered the gold standard for body composition assessment, it is not always feasible for repeated use due to cost, limited availability and radiation exposure. BIA, although validated, may be less precise. Finally, adherence to both RT and protein intake may vary, despite monitoring and counselling, which may influence outcomes.

The ENRICHED trial will implement an innovative protocol combining home-based and supervised RT complemented with whey protein supplementation to improve postoperative outcomes in patients undergoing MBS. Application of evidence-based dietary and RT strategies with accurate monitoring in a real-world clinical setting can potentially contribute to revision of standard clinical care guidelines for a patient-tailored intervention for the preservation of FFM.

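### The reason given for not blinding outcome assessors applies only to patients and treating staff, which leaves avoidable detection bias on tester-dependent secondary outcomes

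*Protocol article*

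**What the plan says.** Under Randomisation, blinding and treatment allocation, the protocol article says: "Blinding of the patients, involved healthcare professionals and outcome assessors is not possible due to the nature of the intervention". No other reason is given.

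Two later statements cover the same ground with different lists of people. The strengths and limitations box says: "Blinding of participants, healthcare providers and researchers is not feasible due to the nature of the intervention, which may introduce performance bias". The Discussion says: "blinding of participants and care providers is not possible due to the nature of the intervention, which may introduce performance bias". Both name performance bias; neither names detection bias.

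On delivery, the section Intervention: home-based and supervised RT says that "weekly RT sessions are provided at the clinic and are supervised by an experienced kinesiologist". Dieticians give the dietary counselling. On assessment, Outcome measures says: "Most outcomes are measured preoperatively and at 3, 6 and 12 months post-MBS".

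Two details of those visits matter. Some questions are put to the patient in person: "These questions address current engagement in RT (eg, type of exercise and frequency), weekly performance of light, moderate and vigorous PA". And under Health-related quality of life, the EQ-5D-5L "questionnaire will be administered orally during each measurement visit to assess HRQoL".

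**The concern.** Training sessions and whey powder cannot be hidden from the patient, the kinesiologist or the dietician. A person who takes a handgrip reading or times a chair-rise at a separate visit is in a different position. The intervention does not tell that person the arm; only knowing it from elsewhere does.

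This matters because several secondary outcomes respond to how the tester behaves. Maximal strength, power and handgrip respond to encouragement, and the SPPB also depends on stopwatch timing. If the tester knows the arm and expects the intervention to work, part of any observed difference may come from the tester, and no analysis can separate that part from a true effect. A larger sample does not help, because this bias does not shrink with sample size.

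**Working it through.** The plan gives no figure on this point, so the check is to set the sections side by side.

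**1. Who does what, and when.**
- Delivery: a kinesiologist at weekly supervised sessions and a dietician at counselling sessions (Intervention sections), from 3 weeks after surgery through week 26.
- Assessment: before surgery and at 3, 6 and 12 months (Outcome measures). Before surgery the intervention has not started. At 12 months, supervised sessions and extra counselling have been over for about 6 months (Follow-up).
- No section says that the same staff must deliver and measure, or that any measurement shows the arm.

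The stated reason therefore covers delivery staff and patients. A staffing constraint might explain unblinded testers, but that would be a different reason, and the article does not give it.

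**2. Are the blinding statements consistent?**

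| Section | Who cannot be blinded | Bias named |
|---|---|---|
| Randomisation, blinding and treatment allocation | patients, professionals, outcome assessors | none |
| Strengths and limitations box | participants, providers, researchers | performance |
| Discussion | participants, care providers | performance |

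Assessors appear by name only in the first, and drop out altogether in the Discussion. Detection bias, the direct consequence of unblinded assessors, appears nowhere.

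**3. Which outcomes can a tester move?**

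| Outcome | Route | Exposure |
|---|---|---|
| Leg strength and power, handgrip | encouragement; the value itself is a device reading | yes |
| SPPB | encouragement, timing, judgement of balance items | yes |
| Åstrand test | tester steps up resistance, but the test is submaximal and estimated from output and heart rate; the data catalogue records results only without beta blockers | smaller |
| EQ-5D-5L | interviewer influence; the respondent is unblinded whoever asks | smaller |
| BIA (primary endpoint) | device reading | little |

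The EQ-5D-5L is collected for the cost-effectiveness work, so interviewer influence on it could carry into the quality-adjusted life years mentioned in the Discussion.

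**4. Do the in-person questions unblind the tester?** Only in part. Controls receive a home-based resistance protocol with 2–3 sessions a week advised, and they are free to train and to take extra protein (both Standard care sections). A control patient can truthfully report regular training. An answer such as weight machines, one of the options in the data catalogue, points towards the intervention arm, whose supervised sessions use four machine-based exercises and one with body weight. The answers hint at the arm without settling it, which also supports the view that a tester could be kept largely unaware of it.

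**The case against.** The strongest reply is that little is at stake. The primary endpoint comes from a device, the lack of blinding is disclosed, and patients remain unblinded, so their own effort and reporting bias persists whoever tests. All of this stands. It limits the point to secondary outcomes and to the tester's share of the bias, but it does not make the stated reason correct.

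Several stronger readings are tempting, and the article does not support them:

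- **That the training questions reveal allocation.** They hint at it, for the reasons in step 4 of the working.
- **That laboratory, DXA and accelerometer processing is unblinded.** The article does not say that those who process these data know the arm. Aliquots go to another institution for storage, and ActivPAL data are processed with software.
- **That the missing order of tests and questions is itself a fault.** A condensed article commonly leaves visit sequence to the full protocol or operating procedures. The order matters here only as a remedy.
- **That the bias has a known size.** The article gives none. Any assumed shift in standard deviations would simply return itself as the apparent effect.
- **That the EQ-5D-5L should move at once to self-completion.** Recruitment began in May 2025. A switch now would give some patients an oral baseline and a self-completed follow-up, while removing only the interviewer's influence.

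It is also fair that the article does not say who does the assessments or how many staff each centre has. Separate testers may not always be available, so that part of the remedy has to be conditional.

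**Conclusion.** The point holds in limited form. The article gives a reason that does not justify unblinded assessors, and its limitations omit the bias that follows. The exposure falls on tester-dependent secondary outcomes: mainly leg strength and power, handgrip and SPPB, and less so the Åstrand test and the EQ-5D-5L. The primary endpoint is little affected and the sample size is untouched. The size of the bias cannot be derived from the article.

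The conclusion assumes that testing can be separated, at least partly, from delivery. Nothing in the article contradicts this, but nothing confirms the staffing. It is a cheap improvement to the plan and does not threaten the trial's main conclusion.

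**What to change.** 1. In Randomisation, blinding and treatment allocation, say that only patients and treating staff cannot be blinded. If testers will know the arm for practical reasons, give those reasons.
2. At each visit, do BIA and the physical tests first, and ask the resistance-training and activity questions afterwards.
3. Ask patients not to tell the tester their arm.
4. Where existing rosters allow, have the tests run by someone who does not train that patient.
5. State that blood, DXA and ActivPAL data are processed under a code that does not show the arm. If this is already practice, one sentence is enough.
6. Keep the EQ-5D-5L mode unchanged for patients already enrolled.
7. Name detection bias in the strengths and limitations box and in the Discussion for whatever stays unblinded, and align the three lists of who is unblinded.

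The cost is a visit-order instruction, some rostering among existing staff and a few sentences of text. Recruitment is expected to run to December 2026 and follow-up lasts 12 months after surgery, so many visits can still benefit. The downsides are that some accidental unblinding will remain and that visits already done were unblinded.
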